### Intervention effectiveness

Residualized change regressions will be used to test for significant differences between the intervention/control groups in change in decisional conflict. Change on the Decisional Conflict subscales, e.g., values or priorities clarification from pre-to post-use at the first session will be the dependent variable. Group (intervention vs. control), baseline decisional conflict and potential confounding variables for which intervention and control groups differ at baseline will be included in the model as independent variables. Longitudinal multilevel models will be used to examine change over time in women’s safety behaviors (percent of safety behavior tried that a survivor found helpful), IPV (measured by the CAS) and substance use (measured by AUDIT and DAST). Time (e.g. baseline, 6 months, and 12 months) will be used as a level 1 predictor of the dependent variable. The level 1 model yields an intercept and slope parameter for each person. The intercept reflects the baseline value on the dependent variable and the slope reflects the rate of change across time on the dependent variable. Group will be used as a level 2 predictor of slope parameter. Finding the group is a significant predictor of the level 1 slope parameters means that individual change over time differs for intervention and control groups. Potential confounding variables for which intervention and control groups are significantly different at baseline will be entered as level 2 covariates predicting individual change.

The same set of analyses described above will be used to examine change in friend’s awareness of IPV, decisional conflict, safety behaviors and confidence to intervene.

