### Outcomes

The primary outcomes for Aim 1 for survivors consist of:*Use of safety strategies*: The Safety Behavior Checklist adapted from Sullivan & Bybee [40] and Parker & colleagues [41] measures the range of strategies used by survivors to halt or escape violence. This instrument asks if each strategy has been used over the last 6 months and if the strategy was helpful in dealing with the abusive partner or abuse. The checklist includes use of formal services (e.g., Have you met/called/texted/instant messaged a professional that works on campus (e.g. a professor, campus administrator, campus staff at a women’s center or campus health clinic) about your partner hurting you (physically, sexually, or emotionally?, Did you get/try to get an order of protection (or restraining order) against your partner?) and informal safety steps (e.g., Have you developed a code/signal so others would know when you were in danger from your partner?, Have you identified a safe place on campus or in the community you could go if your partner became dangerous?). The percent of safety behaviors tried by survivor that she found helpful will be the primary outcome.*Decisional conflict immediately post intervention*: The decision process for survivors is measured with questions adapted from validated subscales of the Decisional Conflict Scale (DCS) [42, 43]. The DCS tests whether using this safety planning decision aid helps a woman to understand the advantages and disadvantages of safety planning options and to know her values related to them. The Decisional Conflict Scale discriminates between people who make decisions and those who delay making decisions. The DCS consists of twelve items (e.g., “I know the risks of taking steps to increase my safety in my relationship”, “I am clear about which benefits of the relationship are most important to me”, “I have enough support from others to make decisions about my safety”) with a 5-point likert response scale from ‘strongly agree’ to ‘strongly disagree’. The DCS provides a total score, which is a measure of the decision process, as well as scores for four subscales (feeling informed, certainty about decision, values clarity, and support), with higher scores on the DCS indicating a greater degree of decisional conflict (indicative of a poorer decision process) [39, 40]. Decisional conflict will be measured pre and post the first use of the decision aid.

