The primary outcomes for Aim 2 for friends of survivors consist of:*Intimate partner violence awareness*: Friends’ awareness of IPV is measured by a 3 scales: 1) Acceptance of General Dating Violence Scale [48], is a five item scale (e.g., There are times in a dating/intimate relationship when violence is okay, Someone who makes their partner jealous on purpose deserves to be hit) with responses on a 4 point scale from strongly disagree to strongly agree; 2) Knowledge of IPV myths is measured with 5 items developed by the research team (E.g. Leaving an abusive partner will stop the abuse, women can’t be abused by a female partner) with responses on a 4 point scale from strongly disagree to strongly agree; and 3) Perception of IPV Awareness and Seriousness are measured with 2 items developed by our team, adapted from items from Beeble et. al [49] (“In your opinion, how *common* are abusive dating/intimate relationships in college? very uncommon, uncommon, happens sometimes, common, very common”, “In your opinion, how *potentially serious* (damaging, harmful, or dangerous) are abusive relationships in college? no potential for danger or harm, generally don’t cause much harm, can have some harmful effects, have harmful effects but generally not serious, potentially very serious or dangerous”).*Confidence to intervene*: Friends’ efficacy to intervene is measured with adaptation of Self-efficacy to Deal with Violence Scale [50] used with adolescents, adapted to assess friends of survivors’ confidence to intervene. The 19-item measure assesses how confident a person feels that they can address relationship issues on a 4 point scale (“not at all confident, somewhat confident, confident, very confident”. Example items include: “How confident are you in your ability to… start a conversation with a friend regarding worrisome behaviors by her partner/ex-partner”, “…identify appropriate/useful resources/people on your campus to help a friend in an unhealthy or unsafe relationship?”.*Friends’ supportive behaviors*: Supportive behaviors are measured with a checklist adapted from multiple sources, including Sullivan & Bybee [40] and Parker & colleagues [41] and from the literature around family/friend responses as described by survivors and engagement behaviors from Latta and Goodman’s [51] model and Beeble et al.’s [49] Approaches to Helping measure. Items ask about what the participant has done to support a friend in an abusive relationship (e.g. let her stay with you for safety reasons, gave her information about relationship abuse resources such as a hotline) and if each behavior was perceived as helpful to the friend.*Decisional conflict immediately post intervention*: The decision process for friends is measured with questions adapted from validated subscales of the Decisional Conflict Scale (DCS) [42, 43] used for survivors for Aim 1. The 12 items test whether using this safety decision aid helps a friend to understand the advantages and disadvantages of options for helping their friend in an abusive relationship, and to know his/her values related to those options (e.g., “I know my options for helping my friend who is in an unhealthy relationship.”, “I am clear about which reasons for helping my friend are most important to me.”, “I have enough advice to make decisions about helping my friend who is in an unhealthy relationship.”

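### Decisional conflict is a primary outcome for survivors and friends, but its dependent variable is an open list of subscales with no deciding score

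*Protocol article*

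**What the plan says.** The Outcomes section places decisional conflict immediately post intervention among the primary outcomes for survivors (Aim 1) and again for friends (Aim 2). On the instrument it says "The DCS consists of twelve items" and "The DCS provides a total score, which is a measure of the decision process, as well as scores for four subscales". The four are given as "feeling informed, certainty about decision, values clarity, and support". It does not say which of these five scores is the primary one. The other survivor primary outcome is treated differently: for safety strategies, the same section fixes one score, the percentage of tried behaviours that the survivor found helpful.

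The analysis is set out under Intervention effectiveness. It opens with the outcome in the singular: "Residualized change regressions will be used to test for significant differences between the intervention/control groups in change in decisional conflict". The next sentence defines the dependent variable: "Change on the Decisional Conflict subscales, e.g., values or priorities clarification from pre-to post-use at the first session will be the dependent variable". The baseline covariate is again singular, baseline decisional conflict. The section closes by extending the approach to friends: "The same set of analyses described above will be used to examine change in friend’s awareness of IPV, decisional conflict, safety behaviors and confidence to" (the quotation stops one word before the end of the sentence). The Mediation analyses section later uses change in decisional conflict, also singular, as a mediator.

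**The concern.** A primary outcome needs one variable, or several with a rule that turns them into one conclusion. Here the dependent variable is plural and defined by example, and the total is not mentioned. Read literally, the analysis gives several regressions for one primary outcome, with nothing stated about which decides, how many must succeed, or at what level each is tested. A reader of the results could not tell whether a significant subscale had been chosen beforehand or afterwards.

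This is more than a detail left to an analysis plan. The article does state the dependent variable, but in terms that fix nothing, whereas it fixes the score for the other survivor primary outcome. The looseness spreads to the baseline covariate and the mediator, neither of which has a single meaning if the outcome is an open set of subscales. It applies in both populations.

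**Working it through.** **The plan's own figure.** The article gives no power or error-rate figure for decisional conflict. Its only power statement (Statistical power) concerns safety behaviours: f = 0.58, 300 per group, autocorrelation 0.3, alpha 0.05, power 0.99. A noncentral F calculation for the group-by-time interaction with N = 600 gives more than 0.999, which is compatible with 0.99. It does not bear on this point.

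**Inputs.**
- Four subscales (Outcomes).
- Alpha 0.05, from Statistical power, assumed two-sided and assumed to apply to each subscale.
- 300 survivors and 300 friends (Recruitment), so 300 / 2 = 150 per arm in each population if allocation is 1:1.
- Correlation r between subscale test statistics: not in the article, so varied from 0 to 0.8.
- Standardized effect d = 0.30: not in the article, used for illustration only.

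**Error rate if any one of four subscales counts.**
- Independent: 1 − (1 − 0.05)^4 = 1 − 0.8145 = 0.185.
- Correlated, by simulating four equicorrelated normal statistics (1,000,000 draws), each tested two-sided at 0.05:

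| r | chance of at least one significant result |
|---|---|
| 0 | 0.186 |
| 0.3 | 0.174 |
| 0.5 | 0.156 |
| 0.7 | 0.130 |
| 0.8 | 0.114 |

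One pre-named score gives 0.05. Counting only results that favour the intervention, the simulated rates are 0.096, 0.087, 0.078, 0.065 and 0.057, against 0.025. Either way, every value is more than double the rate for a single score. If all four stay primary, Bonferroni gives 0.05 / 4 = 0.0125 each.

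**Power of the total against one subscale.** This uses an unadjusted two-sample comparison with 150 per arm. The total is the sum of four subscales of equal variance, so its variance is 4 + 12r in subscale units.
- One subscale with d = 0.30: power 0.74 at 0.05, and 0.54 at 0.0125.
- Effect of 0.30 on all four: total d = 4 × 0.30 / √(4 + 12r) = 0.435, 0.379 and 0.341 at r = 0.3, 0.5 and 0.7. Power is 0.97, 0.91 and 0.84.
- Effect of 0.30 on one subscale only: total d = 0.30 / √(4 + 12r) = 0.109, 0.095 and 0.085. Power is 0.15, 0.13 and 0.11.

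More generally, if k subscales shift equally, the total beats one affected subscale when k > √(4 + 12r). The thresholds are 2.76, 3.16 and 3.52 at r = 0.3, 0.5 and 0.7. So three subscales must move at r = 0.3, and all four at r = 0.5 or 0.7.

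**The case against.** The strongest reply is that this is a condensed article, that a decision rule across subscales commonly sits in the analysis plan, and that the example may be shorthand. An absent multiplicity rule would not be a finding by itself. What stands against the article is narrower: the sentence it does contain defines a primary dependent variable by example and in the plural.

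The error rates are also conditional. The article does not say that all four subscales will be tested at 0.05, or that any one success will count. The figures show what the wording permits, not what the plan declares. This part of the objection stands.

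Several stronger readings are tempting, and the documents do not support them:
- **That the analysis departs from a declared total-score endpoint.** Outcomes calls the total a measure of the decision process, not the primary one, and describes the questions as adapted from subscales. The choice is unfixed; no stated choice is contradicted. Nor does the article use the term co-primary or give a success rule across its primary outcomes.
- **That subscales are weaker tests.** This holds only if the effect spreads over most or all of the scale. If it sits in one subscale, the order reverses sharply.
- **That power should be computed at 120 per arm, 150 less 20%.** The 20% belongs to a power analysis of change from baseline to 12 months. This outcome is measured before and after first use. Some loss before baseline completion is possible, but no rate is given.
- **That the example was picked to favour the intervention.** Values clarification does resemble MyPlan's priority-setting exercise, and the control plan is not personalized to priorities. But nothing says that this subscale will decide the outcome.

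**Conclusion.** The concern holds as a badly fixed analysis of a primary outcome in both populations. As written, one primary outcome can give several unadjusted tests. If any one of four counted, the false-positive chance in each population would lie between about 11% (r = 0.8) and 18.5% (independent), against 5% for one score. The independent figure needs only four tests at 0.05; the rest depend on assumed correlations. The power comparison does not show that the total is always better. It shows that the better score depends on where the effect falls, which is why the score must be named beforehand. The point should be corrected, but it calls neither the design nor the sample size into question.

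**What to change.** Under Intervention effectiveness, state that the primary decisional-conflict analysis, for survivors and for friends, is the residualized-change regression on the DCS total score from before to after first use, with the baseline DCS total as covariate. Report the four subscales as supportive results. The same sentence gives the singular baseline covariate one meaning; using the total for the mediator as well would settle that too.

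If the sponsor expects the effect mainly in one area, two alternatives are acceptable: name the deciding subscale in advance, or keep all four as primary with a multiplicity adjustment, for example 0.0125 each. In the illustration above, the second option lowers single-subscale power from 74% to 54%.

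The cost is a sentence, with no change to data collection or sample size. The real downside of the total is dilution. At 150 per arm and d = 0.30, an effect confined to one subscale would be detected with about 11–15% power on the total, against 74% on that subscale. An equal effect on all four favours the total, 84–97% against 74%. The supportive subscale results would still show a confined effect, but not as the primary conclusion.

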### Mediation analyses

Additionally, change in decisional conflict will be tested as a mediator of the relationship between the intervention and safety behaviors at 12 months for both survivors and friends of survivors using a series of regressions. Sobel’s test will be used to estimate the mediation effect. The product coefficient Approach associated with the Sobel’s test has been found to be a powerful method for estimating indirect effects [59]. The mediation effect and associated boot-strapped 95 % confidence intervals will be estimated. Separate analyses will be conducted for the women and friends. A similar approach will be used to test safety behaviors at 12-months as a mediator of the relationship between the intervention and change from baseline to 12-months in IPV for the women and confidence to intervene for friends.

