## Data analyses

Before any analyses are carried out, the data will be audited for quality and completeness, including missing data patterns, evaluation of distributions for outliers in quantitative data, and checking distributions of variables to ensure that they meet the assumptions of planned analyses. Chi-square tests for categorical variables and t-tests for continuous variables will be used to test for differences between the safety intervention and control groups on baseline variables that are potential confounding variables. These included relationship status (dichotomous: currently residing with the abuser or not); language (English or Spanish), baseline knowledge of safety options (continuous); clarity of safety preferences (continuous); perception of support (continuous); computer experience (continuous). Variables for which significant differences are found will be included as covariates in the analyses where appropriate. All analyses will use intent-to-treat principles.

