### Dose response analyses

We will examine the relationship between the number of times or “dose” the App is used during the year and change from baseline to 12-months in the main outcomes of safety behaviors and IPV using multiple regression. We will control for baseline scores on the outcome measures in this analysis as the level of use of the App may depend on severity of violence. This analysis will examine if repeated use of the App results in greater improvement in the outcome scores.

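### The mediation analyses name no baseline scores, and the only covariate rule that reaches them selects on arm imbalance, which leaves the mediator-to-outcome path open to bias and lost power

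*Protocol article*

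**What the plan says.** The section on mediation analyses states that "change in decisional conflict will be tested as a mediator of the relationship between the intervention and safety behaviors at 12 months", for survivors and for friends, "using a series of regressions". Sobel's test and a bootstrapped 95% confidence interval follow. A second mediation takes safety behaviors at 12 months as mediator and change from baseline to 12 months in IPV as outcome. For friends, the outcome is confidence to intervene. Neither mediation names a baseline covariate.

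Three other places bear on this:

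- Intervention effectiveness: "Residualized change regressions will be used to test for significant differences between the intervention/control groups in change in decisional conflict". Of the predictors it says "Group (intervention vs. control), baseline decisional conflict and potential confounding variables for which intervention and control groups differ at baseline will be included". This covers the effect of arm on conflict. It does not cover the regression of behaviors on conflict.
- Data analyses, opening paragraph: "Variables for which significant differences are found will be included as covariates in the analyses where appropriate". The candidates listed are relationship status, language, knowledge of safety options, clarity of preferences, perceived support and computer experience. Baseline safety behaviors and baseline IPV are not among them.
- Dose response analyses: "We will control for baseline scores on the outcome measures in this analysis". Here the baseline outcome is named, with the reason that App use may depend on how severe the violence is.

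Under Outcomes: "Decisional conflict will be measured pre and post the first use of the decision aid". The mediator therefore has its own baseline.

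**The concern.** Randomisation protects the path from arm to mediator. It does not protect the path from mediator to outcome, because nobody is randomised to a level of conflict or of safety behavior. Two features make baseline scores matter here.

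First, a change score is normally correlated negatively with its own starting value. If starting conflict is related to starting safety behaviors, and these persist to 12 months, change in conflict is associated with 12-month behaviors even when conflict has no effect on them.

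Second, the stated covariate rule selects variables on which the arms differ. Under randomisation each candidate passes such a test about 5% of the time (taking the test at the 5% level), however strongly it confounds mediator and outcome.

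Aim 1 hypothesises a chain: less decisional conflict leads to more safety behaviors and less IPV. The mediation section is the only place where the links of that chain are tested. At stake are a missed pathway in the first mediation and a spurious one in the second.

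**Working it through.** The document gives no figure for the mediation analyses, so there is none to reproduce.

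**Inputs from the document.** 300 survivors and 20% attrition: 300 x 0.8 = 240 analysed. Alpha is 0.05 (stated for the group-by-time test, assumed here for a two-sided Sobel test).

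**Assumptions, none from the document.** Normal scores with unit SD before and after first use; pre-post conflict correlation 0.6; App effect on conflict a = -0.5 SD; baseline-to-12-month behavior correlation 0.5; baseline conflict-behavior correlation r0 varied.

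**First mediation, closed form.** Let b be the slope of 12-month behavior on post-use conflict, and g the association of baseline conflict with 12-month behavior other than through post-use conflict. With pre-post correlation p, within arm:

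- Var(post - pre) = 2(1 - p)
- Cov(post - pre, behavior) = (1 - p)(b - g)
- slope on unadjusted change = (b - g)/2

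With baseline conflict in the model, the slope is b.

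No true mediation (b = 0, g = 0.5 x r0):

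- r0 = -0.1: slope 0.025, indirect effect -0.5 x 0.025 = -0.0125
- r0 = -0.3: slope 0.075, indirect effect -0.0375
- r0 = -0.5: slope 0.125, indirect effect -0.0625

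Simulated means are -0.013, -0.041 and -0.062. Sobel rejection is 4%, 13% and 28%. Bootstrap rejection is 5%, 23% and 38%, against 5-6% with both baselines. These false effects are negative, the opposite of what Aim 1 hopes for.

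True effect of -0.2 acting through the part of post-use conflict not predicted by baseline (g = 0.12 + 0.5 x r0; true indirect effect -0.5 x -0.2 = 0.10):

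- r0 = 0: slope (-0.2 - 0.12)/2 = -0.16, indirect effect 0.08
- r0 = -0.3: slope (-0.2 + 0.03)/2 = -0.085, indirect effect 0.0425

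Sobel power at 240:

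| Regressions | r0 = 0 | r0 = -0.3 |
|---|---|---|
| Change score, no baseline | 47% | 13% |
| Baseline conflict in the arm-to-conflict regression only | not reported | 14.5% |
| Residualized change as mediator | 59-61% | 59-61% |
| Both baselines in both regressions | 71-75% | 71-75% |

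Row two matters: carrying the Intervention effectiveness model into the first regression alone repairs nothing, because the bias sits in the second.

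Sensitivity (bootstrap power at r0 = -0.1 / -0.3 / -0.5):

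- effect through post-use level: 17% / 7% / 7%, against 77-81% adjusted
- effect through raw change: 71% / 38% / 18%, against 76-83% adjusted

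**Second mediation, survivors, no true effect.** Let r be the baseline IPV-behavior correlation, with stability 0.5 for both behaviors and IPV and an App effect on behaviors of 0.4 SD (the middle of an assumed 0.3-0.5). The slope of IPV change on 12-month behavior is -(0.5r)(1 - 0.5) = -0.25r.

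- r = 0.3: slope -0.075, indirect effect 0.4 x -0.075 = -0.03
- r = 0.5: slope -0.125, indirect effect -0.05

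A negative value reads as the App lowering IPV through safety behaviors. Sobel rejection is about 7% at r = 0.3 and 22-24% at r = 0.5, against about 2% with both baselines.

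For friends, the same formula with a positive baseline correlation between supportive behaviors and confidence also gives a negative slope. There it works against the hypothesis.

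**The case against.** The strongest reply is that the text nowhere says the change is raw or that baselines are left out. The preceding section analyses the same quantity by residualized change with baseline conflict as a predictor, and the dose-response section adjusts for baseline too. A journal article may leave the covariate list of a supporting analysis to a fuller document. The group comparisons on conflict, behaviors and IPV are untouched. Every size above rests on assumed correlations.

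Much of this stands. A reader might infer that the plan fixes a raw, unadjusted change score; that is silence, not a statement. If a residualized score is used as mediator, the bias in the first mediation disappears.

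What does not fall away is the covariate rule, which is stated and uses the wrong criterion for mediator-outcome confounding. The residualized reading also does not help the second mediation, since change in IPV is modelled elsewhere by multilevel slopes. Even on the favourable reading, power is about 60% where 71-75% is available from data already collected.

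**Conclusion.** The point holds as a specification to settle, not as proof of a defective test. The mediation section names no baseline scores, and the one rule that would bring covariates in selects on arm imbalance. Without the baseline, the conflict-to-behavior path is biased by an amount and sign that depend on an unreported correlation. Under zero or negative correlation the main harm is a missed pathway: Sobel power 13-47% against 71-75%. In the survivors' second mediation, a false effect in the hypothesised direction appears in about 7-24% of trials against 2%. On the residualized reading, the first mediation only loses power.

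Three stronger readings are tempting and unsupported:

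- That the test measures regression to the mean instead of mediation. Randomisation still protects the arm-to-conflict path, and when the App does not move conflict, rejection stays at or below about 3%.
- That a true pathway would be reported as its reverse. The sign flips only when g is more negative than b. With b = -0.3 and g = -0.35 the slope is (-0.3 + 0.35)/2 = 0.025, and rejection is only 4-6%.
- That the first mediation would invent the Aim 1 pathway. A false effect in that direction needs a positive baseline correlation, and nothing in the document indicates one.

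**What to change.** In the mediation section, state the following:

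- First mediation: both regressions (arm to mediator; mediator and arm to outcome) include baseline decisional conflict and baseline safety behaviors, or baseline supportive behaviors for friends. With baseline conflict in the model, change and post-use score give the same indirect effect, so raw versus residualized no longer matters.
- Second mediation: both regressions include baseline safety behaviors and baseline IPV for survivors, or baseline supportive behaviors and baseline confidence for friends.
- These terms enter regardless of any baseline test between arms.
- The conclusion rests on the already planned bootstrapped 95% interval of the adjusted indirect effect.

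The cost is a change of wording and two degrees of freedom per regression. The follow-up sessions repeat the baseline questions, so the scores are already collected and no participants are added. Adjustment for these baselines does not remove unmeasured mediator-outcome confounding, so the mediation results should still be reported with that caveat.
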